## Abstract

**Introduction:**

Atrial fibrillation (AF) is the most common sustained arrhythmia worldwide, associated with significant morbidity, mortality and healthcare utilisation. AF rhythm control strategies demonstrate attrition with time. A number of modifiable AF risk factors contribute to an atrial cardiomyopathy culminating in incident AF but importantly also recurrence. We propose that a novel multidisciplinary lifestyle intervention (Super Rehab, SR) may improve symptoms and AF burden.

**Methods and analysis:**

This is a single-centre, randomised controlled study. Patients aged ≥18 years with a body mass index ≥27 kg/m^2^ with paroxysmal or persistent AF will be randomised 1:1 to National Health Service (NHS) usual care (UC) or to SR (together with NHS UC). SR incorporates high-intensity exercise, personalised dietary advice and AF risk factor modification. SR will be undertaken over 12 months. In addition to baseline assessments, follow-up assessments will occur at the 6, 12 and 15-month time points. The primary outcome will be the difference in AF symptom burden at 12 months between groups. Secondary outcomes include AF burden (assessed by an implantable cardiac monitor), changes to cardiac structure and function and computed tomography-based assessment of epicardial adipose tissue.

**Ethics and dissemination:**

Ethics approval was granted by London-Chelsea Research Ethics Committee (reference: 22/LO/0479 22/08/2022). All participants will provide written informed consent prior to enrolment. Study findings will be disseminated via presentations to relevant stakeholders, national and international conferences and open-access peer-reviewed research publications. A summary will also be communicated to the participants.

**Trial registration number:**

ClinicalTrials.gov ID NCT05596175.

Strengths and limitations of this studyRandomised controlled study examining the impact of a novel lifestyle intervention (Super Rehab) on atrial fibrillation (AF) in an National Health Service setting.Super Rehab combines 1:1 high-intensity interval training with resistance exercises and 1:1 dietary review sessions over a 12-month programme.Robust data on AF burden will be generated through the use of implantable cardiac monitors.Any cardiac structural and functional changes will be assessed with both echocardiography and CT coronary angiography.This is a single-centre study, which may affect its external validity.

## Introduction

 Atrial fibrillation (AF) is the most common sustained cardiac dysrhythmia occurring with increasing incidence and prevalence.^1 2^ It affects approximately 1.5 million people in the UK.^3^ AF imparts a significant health burden, most notably heart failure and stroke, in addition to conferring a 1.5–1.9-fold mortality r isk.^4^,^7^It is estimated that by 2040 AF direct care costs alone could constitute 4.3% of the entire National Health Service (NHS) budget.^8^

Current AF strategies targeting restoration of normal sinus rhythm include medications and interventional procedures such as direct current cardioversion (DCCV) and/or AF catheter ablation (CA).^9 10^ Current anti-arrhythmia medications demonstrate modest therapeutic benefit^11^ with safety considerations and side effect profiles often limiting their use.^11 12^ Despite the increasing incidence of AF, the introduction of novel anti-arrhythmic based therapy has not been forthcoming. DCCV requires a day case hospital admission and administration of anaesthetic. There is a significant recurrence rate with approximately 76% of patients returning to AF 1 year following DCCV.^13^ CA technology has improved with time^14^ but remains a costly invasive procedure.^15^ Overall complication and severe complication rates are approximately 4.5% and 2.5%, respectively.^16^ With a single AF ablation procedure, recurrence over longer-term outcomes (≥3 years) has been reported at 47%.^17^

There is increasing evidence that cardiometabolic risk factors are responsible for electromechanical alterations in the atrial myocardium leading to an atrial cardiomyopathy.^18^ This not only provides a mechanistic pathway to AF onset, but if not addressed, the substrate to recurrence, thereby representing a crucial target in the secondary prevention of AF. A system of solely targeting rhythm restoration without systematically treating the underlying drivers of AF is therefore sub-optimal.

### Arterial hypertension

Hypertension is present in 60%–80% of patients with established AF.^19^ Experimentally induced hypertension has been shown to cause left atrial hypertrophy, fibrosis and inflammation resulting in greater AF inducibility and duration.^20^ It confers a 150% greater chance of progressing from paroxysmal to persistent AF.^21^ Optimal blood pressure increases the freedom from AF following ablation.^22^

### Sleep disordered breathing (SDB)

Sleep disordered breathing (SDB) is highly prevalent in patients with AF.^23^ Hypoxaemia, hypercapnia and changes to sympathetic tone result in left atrial remodelling.^24 25^ AF-free survival following DCCV^26^ and AF ablation^27^ is reduced in those with SDB. Treatment of SDB reduces recurrence rates.^26^

### Hyperglycaemia

Electrical remodelling and myocardial fibrosis occur with hyperglycaemia.^28 29^ Poor glycaemic control prior to ablation is associated with a higher recurrence rate and indeed improvements in haemoglobin (HbA1c) pre-ablation have been shown to increase AF free survival.^30^

### Body mass index (BMI)

In the UK, one in four adults is obese, with a rising prevalence.^31^ Obesity increases left atrial size and epicardial adipose tissue volume (EAT).^32^ Such changes in the metabolically active EAT has been shown to result in the release of pro-inflammatory and pro-fibrotic mediators into the underlying myocardium.^32^ From a secondary care point of view, obesity has been shown to increase the recurrence rate of AF following catheter ablation,^33^ and weight loss prior to ablation improves freedom from AF.^34 35^

### Exercise and fitness

In addition to weight loss, improvements in physical fitness provide a synergistic effect. CARDIO-FIT (impact of cardiorespiratory fitness on arrhythmia recurrence in obese individuals with AF) demonstrated that an improvement of ≥2 metabolic equivalents conferred a 200% higher probability of AF-free survival over a 5-year follow-up period.^36^ Moreover, higher cardiorespiratory fitness is associated with a lower long-term all-cause mortality in patients with AF.^37^

### Previous work

Several studies have shown an improvement in AF burden and symptoms with weight reduction and risk factor modification.^38^,^40^ These studies however were predominantly cohort studies rather than randomised controlled trials and were undertaken in non-UK, non-NHS populations. There has been insufficient focus on combining supervised exercise and nutrition interventions together with risk factor modification. Our intervention will target a holistic approach to AF management with community-based personal trainers (PRs) and NHS dietitians. Additionally, much of the previous work has focused on patients at a tertiary referral centre at the time of an ablation rather than earlier in the referral process where we plan to recruit. The impact of an intervention on AF burden has also frequently been reported using intermittent ambulatory monitoring. This provides an incomplete assessment of overall AF burden. Our work will use an implantable cardiac monitor (ICM) for the duration of the study providing a detailed breakdown of the dysrhythmia burden.

### Aims and objectives

We aim to establish whether a structured cardiovascular rehabilitation intervention (Super Rehab (SR)), which targets AF risk factors, weight loss and greater physical fitness, leads to an improvement in symptoms for patients with AF in whom a rhythm control management strategy has been chosen.

### Primary objectives

1. To assess the difference in AF symptom burden (score range 0–35), as defined by the University of Toronto AF severity scale (AFSS), between usual NHS usual care (UC) and SR groups at 12 months. Additional evaluations will be conducted and reported at the 6- and 15-month time points.

### Secondary objectives

To assess the difference in % AF burden between groups at 12 months, with additional evaluations conducted and reported at the 6- and 15- month time points.The assess the total duration and frequency of AF episodes between groups at 12 months, with additional evaluations conducted and reported at the 6- and 15-month time points.To assess time to first AF recurrence following a DCCV or ablation (where ICM data is available prior to intervention)To assess the change in the following cardiac and metabolic parameters between groups at 12 months, with additional evaluations conducted and reported at the 6- and 15-month time points:

Weight, body mass index (BMI), waist circumferenceCardiorespiratory fitnessVisceral fatLeft atrial size and strain.Peri-atrial fat volume and atriomic signal.Systolic and diastolic blood pressureLow density lipoprotein, high density lipoprotein, total cholesterol, glycated HbA1c and C-reactive protein% of time active.

5. To assess the difference in the following patient-reported outcomes between groups at 12 months, with additional evaluations conducted and reported at the 6- and 15-month time points:

European Heart Rhythm Association (EHRA) scaleAtrial fibrillation effect on quality of life (AFEQT)EuroQol-5 dimensions-5 levels (EQ-5D-5L)Hospital Anxiety and Depression Scale (HADS)Holistic capability assessment using the ICEpop CAPability measure for Adults (ICECAP-A).NHS resource-use questionnaire.

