### Sample size

We aim to recruit 36 patients. The sample size was estimated using a one-tailed two independent sample t-test with a standardised effect size of 0.93 (estimated using a previous publication in a similar population using the same assessment methodology)^40^ with an alpha of .05 and power of .80 producing a sample size of 30 to detect a difference in AF symptom score. A 20% drop-out rate has been factored in to give a total sample size of 36 randomised 1:1.

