On successful completion of the baseline assessments, all participants will have an ICM inserted subcutaneously to monitor AF burden for the duration of the study (Biomonitor IIIm, Biotronik SE and Co. KG). Although ICM implantation is invasive, the procedure is low risk, and participants will be closely monitored throughout the study to minimise any potential complications. ICM has been used in numerous AF studies, and they represent the gold standard of rhythm monitoring. Additional informed consent will be obtained for the implantation procedure. The device will be removed on completion of the study.

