### Randomisation

Participants will then be randomised to either UC or SR using a web-based platform (Sealed Envelope: https://www.sealedenvelope.com/) in permuted blocks of four using an allocation sequence generated at random. Stratification will be by AF subtype (paroxysmal or persistent). Participants’ general practitioners will be informed of their patients’ involvement in the study and will be provided with a study information sheet.

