### Data analysis

The distributional properties of the continuous variables will be examined by plots. Participant baseline characteristics and health outcomes will be summarised (including missing data) using descriptive measures: mean (SD) or median (IQR) for symmetric or skewed continuous variables, respectively; number (percent) for categorical variables; and mean (SD) absolute and percent change for longitudinal data will be reported separately by treatment allocation.

The primary outcome, change in AF symptom score, will be assessed using a two-way analysis of covariance (ANCOVA) adjusted for baseline score and AF type using data from subjects where both baseline and follow-up data are complete. The impact of missing follow-up data on the primary analysis will be explored with sensitivity analysis using methods such as last observation carried forward. This approach is likely to provide a conservative estimate of treatment effects. A prespecified secondary analysis will include a two-way ANCOVA for change in AF symptom score at 6 months, again adjusted for baseline score and AF subtype. To aid interpretation, changes will be considered in light of the minimally clinically important difference (MCID). While an anchor-based MCID has not yet been formally established for the AFSS, changes of approximately 3–5 points are considered clinically meaningful in analogous AF-specific instruments, such as the AFEQT. This range will be used to contextualise the clinical relevance of observed changes.

For continuous secondary outcomes, two independent samples t-tests or non-parametric alternatives will be used. Parametric assumptions will be checked by reviewing univariate histograms prior to formal analysis. For categorical secondary outcomes, change in status at follow-up will be compared between groups using χ² or Fisher’s exact test. Time to AF recurrence and event-free survival curves will be with Kaplan-Meier assessment and differences between curves tested with the log-rank test.

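### The planned tests of the implantable-monitor outcomes leave out AF subtype, the randomisation stratum; this makes them conservative and can cost much power if burden differs strongly by subtype

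*Protocol article*

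**What the plan says.** The Secondary objectives list "To assess the difference in % AF burden between groups at 12 months" and "the total duration and frequency of AF episodes between groups at 12 months", each also to be evaluated at 6 and 15 months. Both AF types are enrolled. Under Randomisation: "Stratification will be by AF subtype (paroxysmal or persistent".

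The Data analysis section adjusts the symptom score, at 12 and at 6 months, for baseline score and AF type. Continuous secondary outcomes get a two-group t-test or a non-parametric substitute, with no AF-type term. The choice between them rests on plots: "Parametric assumptions will be checked by reviewing univariate histograms prior to formal analysis".

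Under Baseline assessments: "On successful completion of the baseline assessments, all participants will have an ICM inserted subcutaneously". The Randomisation section follows directly and no run-in recording is mentioned. A pre-randomisation burden value to adjust for is therefore not evident.

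**The concern.** AF subtype describes how much of the time a patient is in AF, so it is likely to predict device-recorded burden at least as well as it predicts symptoms. Stratified blocks balance it between the arms. If the analysis then ignores it, the difference between subtypes stays in the error variance although it no longer contributes to chance differences between arms. The standard error is too large, the test rejects less often than its nominal level, and a real reduction in burden is easier to miss. The article names ICM data on AF burden as a strength of the study, so the loss matters.

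Episode frequency raises a separate point. A patient in continuous AF has one episode and a patient with many brief paroxysms has many. A move from continuous to intermittent AF raises the count while burden falls.

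**Working it through.** **1. The plan's own figure.** The Sample size section uses a "one-tailed two independent sample t-test" "with a standardised effect size of 0.93", "with an alpha of .05 and power of .80 producing a sample size of 30 to detect a difference in AF symptom score". With 15 per arm, one-sided power is 79.9%, so 30 is reproduced; 30 × 1.2 = 36. Two-sided power at 15 per arm is 69%. This concerns the symptom score only. No effect, SD, subtype mix or power is stated for any ICM outcome, so everything below rests on assumptions.

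**2. Formula.** Let p be the persistent share and r the gap between subtypes in within-subtype SDs. Without an AF-type term the variance is multiplied by v = 1 + p(1 − p)r², and the effective standardised effect is d/√v. I borrow d = 0.93 for illustration, with p = 0.5, 15 per arm and two-sided 5%.

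| r | v | effective d | power, standard formula |
|---|---|---|---|
| 0 | 1.00 | 0.93 | 69% |
| 1 | 1.25 | 0.832 | 60% |
| 2 | 2.00 | 0.658 | 41% |
| 3 | 3.25 | 0.516 | 28% |

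The standard formula treats the subtype gap as noise in the difference as well as in its standard error. Under balanced strata only the standard error is inflated. Approximately, power is Φ(0.93√7.5 − 2.048√v) and null rejection is 2Φ(−2.048√v), where 2.048 is the t critical value on 28 df and 0.93√7.5 = 2.547.

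- r = 1: power Φ(2.547 − 2.290) = 60%; null rejection 2.2%.
- r = 2: power Φ(2.547 − 2.896) = 36%; null rejection 0.4%.
- r = 3: power Φ(2.547 − 3.692) = 13%; null rejection 0.02%.

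**3. Simulation with a wide gap.** 32 participants, 8 per arm per subtype. Logit burden is N(−3, 1.2) in paroxysmal and N(1.5, 1.2) in persistent AF (SD 1.2), which gives medians of 4.7% and 82%. Super Rehab lowers the logit by 1. Two-sided 5%, up to 3,000 replicates; ranges are across repeated runs.

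| Scenario | t-test | Mann-Whitney | van Elteren |
|---|---|---|---|
| No effect | 0% | 0% | 4–5% |
| Shift 1, no reversion | 1% | 2–3% | 57–60% |
| Shift 1.5, no reversion | 8–9% | 18–20% | 90–91% |
| Shift 1, 25% of persistent at low burden | 4% | 13–14% | 41–42% |
| Shift 1, 50% | 7% | 23–26% | 35–37% |
| Shift 1, 75% | 9% | 38–40% | 41–42% |

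**4. A second model.** Beta-distributed burden, N = 30, 1,000 runs.

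| Mean burden, paroxysmal/persistent | Persistent share | Relative reduction | t-test | Mann-Whitney | Linear model with AF type | van Elteren |
|---|---|---|---|---|---|---|
| 10/90% | 50% | 30% | 4% | 5% | 53% | 57% |
| 10/90% | 50% | 50% | 40% | 30% | 89% | 87% |
| 10/50% | 50% | 50% | 28% | 26% | 45% | 54% |
| 20/40% | 50% | 50% | 34% | 41% | 39% | 49% |
| 20/40% | 50% | 30% | 14% | 13% | 17% | 18% |
| 10/90% | 80% | 50% | 89% | 94% | 98% | 99% |

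Under no effect the unstratified tests rejected in 0% to 4% of runs. Across all scenarios of this model at N = 30, including a 20% persistent share, unstratified power ranged from 1% to 94% and stratified power from 12% to 99%. Van Elteren exceeded both unstratified tests in each scenario.

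**5. Episode count.** No arithmetic is needed. % burden and total duration rise with time in AF. The count does not: it is 1 for unbroken AF and high for frequent short episodes.

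**The case against.** The strongest reply is that the very low power figures come from an unfavourable set-up: an even mix, no persistent patient leaving high burden, and a moderate effect. Every participant has been referred for ablation or cardioversion, so many persistent patients may spend part of follow-up in sinus rhythm. This stands. A reader might infer that the burden comparison is nearly powerless; the article does not support that as a general statement, since it gives no gap, mix or effect. Where the subtypes are close, power is low mainly because 30 to 36 patients were sized for the symptom score. Equally, the gap need not close: the Introduction cites about 76% back in AF a year after cardioversion.

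It can also be said that a stratified rank test is itself non-parametric, and that such detail belongs in a fuller document. This stands only in part. The same section names AF type for the symptom score and then states a two-group comparison without it for the other continuous outcomes, so a method is stated and not merely left open.

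There is no false-positive risk; the loss is one of efficiency on secondary outcomes.

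Two further inferences should be resisted. Burden is not labelled a key outcome, nor is it the only objective one: time to recurrence, exercise testing and left atrial measures are also planned. And the article never says that a higher episode count means worsening. It lists frequency beside duration and % burden, so one cannot claim that the trial will misread it.

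**Conclusion.** The concern holds in a conditional form. The stated tests for the ICM outcomes omit a factor that the design stratifies on and that the symptom-score analysis adjusts for. They are therefore conservative whenever burden differs by subtype. The power cost runs from severe (about 2–3% against about 60% for the rank tests, with medians of about 5% and 82%, an even mix, a one-logit effect and no reversion) to almost nil (about 40% against 42% when 75% of persistent patients revert). Which end applies cannot be told from the article. The stratified rank test did at least as well in every scenario examined, with null rejection near 5% in the wide-gap model, so including the stratum carries little risk. Pooled episode frequency is not a measure of AF exposure and should not be interpreted alone.

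**What to change.** In the Data analysis section, replace the histogram-led choice of an unstratified test for the ICM outcomes:

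- Analyse % AF burden, and total duration as a percentage of monitored time, by a van Elteren test or a rank ANCOVA with AF type. Report a stratified Hodges-Lehmann difference with its 95% CI. Put this way, duration largely repeats % burden, so the two should not be read as independent confirmation.
- Report episode frequency as a rate per monitored day within AF subtype, and interpret it alongside burden.

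The cost is analysis-plan wording; no patients, visits or data are added. The small downside is less inference on pooled episode frequency. Recruitment is complete and final data collection was expected by November 2025, so the change should be dated and made before outcome data are examined by arm.

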**Figure 2 F2:**
[figure not shown]
The Super Rehab programme.

*Dietetics*
Once randomised to the intervention arm, participants will receive a SR introductory educational booklet which includes the aims of SR in addition to structured dietary and exercise advice. A dietitian will work with participants using photographic diet diaries to identify areas for improvement. They will provide tailored advice through the study to identify and remove any residual barriers to dietary improvements. Dietitian sessions will take place either face-to-face or remotely depending on participant preference.ExerciseParticipants will undertake both supervised (with a PT) and homework-based exercise sessions. PT supervised sessions will consist of resistance training and high-intensity interval training using the Norwegian 4×4 model.^44^ Baseline CPET results for each participant will help provide guidance to set exercise intensity parameters. The PT will additionally prepare suggested homework exercises. PT-led sessions will be undertaken at a local gym facility.AF and risk factorsA 3-monthly clinical review delivered by an arrhythmia specialist nurse will aim to improve cardiospecific AF risk factors including lipid targets, glycaemic control and blood pressure control. SDB will be screened for and referred for further review as necessary. AF rhythm control strategy will be reviewed and heart rate controlled in line with guidance. Clinical review sessions will take place remotely.

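### The log-rank test of time to AF recurrence after DCCV or ablation covers only participants who have a procedure after randomisation, so it is not a randomised comparison of SR with UC

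*Protocol article*

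**What the plan says.** The third item under Secondary objectives is "To assess time to first AF recurrence following a DCCV or ablation (where ICM data is available prior to intervention"). The Data analysis section gives the method: "Time to AF recurrence and event-free survival curves will be with Kaplan-Meier assessment and differences between curves tested with the log-rank test".

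The order of events is fixed elsewhere. The text on the implantable cardiac monitor (ICM) says "On successful completion of the baseline assessments, all participants will have an ICM inserted subcutaneously", and the Randomisation section follows with "Participants will then be randomised to either UC or SR using a web-based platform". Randomisation is stratified by AF subtype only.

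The Inclusion criteria require a referral for ablation and/or DCCV through routine care. They do not require that the procedure takes place.

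Two further statements bear on who goes on to a procedure:
- Within SR, the 3-monthly specialist-nurse review includes this: "AF rhythm control strategy will be reviewed and heart rate controlled in line with guidance".
- The Patient and public involvement section explains the choice of primary outcome by saying that symptoms commonly determine rhythm-control decisions, including the step up to invasive treatment.

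The Introduction cites "approximately 76% of patients returning to AF 1 year following DCCV" and, after a single ablation, "recurrence over longer-term outcomes (≥3 years) has been reported at 47" per cent.

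**The concern.** A participant enters this analysis by having a procedure. That happens after allocation, and the article gives two routes by which allocation can influence it: SR is meant to reduce the symptoms that prompt procedures, and SR contains a scheduled review of rhythm strategy. If SR spares milder patients a procedure, those left in the SR curve are the harder cases. The better SR works on symptoms, the less alike the two procedure subsets become.

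A second difficulty is procedure type. If DCCV and ablation are analysed together, a difference in mix between arms produces a difference between curves even when SR has no effect on recurrence. Randomisation is not stratified by planned procedure, so in a trial of 36 the mix can also differ by chance.

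At stake is what may be concluded. A small p-value could arise with no SR effect on recurrence, and a real effect could be hidden.

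**Working it through.** **No planned figure to reproduce.** The article's only sample size concerns the symptom score: one-sided alpha 0.05, power 0.80, effect size 0.93. The normal approximation gives 15 per arm, 30 in total, and 30 × 1.2 = 36. Nothing is sized for recurrence.

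**Step 1, order of events.** Baseline assessments, then ICM insertion, then randomisation. The outcome needs ICM data before the procedure. A qualifying procedure therefore follows insertion and, barring an exceptional case in the short gap, follows randomisation.

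**Step 2, procedure mix.** Inputs from the Introduction: DCCV 76% at 1 year; ablation 47% at 3 years or more, taken here as 3 years. Assumption: constant hazards.
- DCCV hazard: −ln(1 − 0.76) = 1.43 per year.
- Ablation hazard: −ln(1 − 0.47)/3 = 0.21 per year, so 1-year recurrence is 1 − exp(−0.2116) = 19.1%. The hazard ratio is 1.427/0.2116 = 6.7.
- One-year recurrence with DCCV share q: 0.76q + 0.191(1 − q).

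The opposite extreme puts all 47% in year 1. The formula becomes 0.76q + 0.47(1 − q), and the hazard ratio is 1.427/0.635 = 2.25. The shares below are assumed; the article gives none.

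| DCCV share, UC / SR | Constant hazard, UC v SR | All 47% in year 1, UC v SR |
|---|---|---|
| 70% / 50% | 58.9% v 47.5% | 67.3% v 61.5% |
| 80% / 40% | 64.6% v 41.8% | 70.2% v 58.6% |

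Every gap arises from mix alone, with no SR effect on recurrence after either procedure.

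**Step 3, selection alone.** Simulation with no SR effect on recurrence. Assumptions: severity is standard normal; the log-odds of having a procedure rise by 1 per SD of severity; uptake is 80% in UC; the recurrence hazard is 1.43 per year × exp(b × severity); follow-up is 6 months.

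| SR uptake | SR/UC rate ratio, b = 0.5 | SR/UC rate ratio, b = 1.0 |
|---|---|---|
| 80% | 1.00 | 1.00 |
| 60% | 1.08 | 1.14 |
| 40% | 1.17 | 1.30 |

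**Step 4, precision.** If 40% to 100% of 36 have a procedure and 50% to 76% of those recur, events number from 36 × 0.4 × 0.50 = 7.2 to 36 × 1.0 × 0.76 = 27.4. With equal arms:
- The standard error of the log hazard ratio is 2/√events, from 0.75 down to 0.38.
- Two-sided log-rank power for a hazard ratio of 0.5 is Φ(√events × 0.693/2 − 1.96), from 15% to 44%.
- Events needed for 80% power: 4 × (1.96 + 0.84)² / 0.693² ≈ 66.

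**The case against.** Several points on the other side stand.

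- **Referral precedes enrolment.** A reader might infer that whether and which procedure a participant has is settled wholly after randomisation. The article does not support that: all participants are already referred, and a rhythm-control strategy has been chosen. What remains open is whether the procedure goes ahead, when, and whether the plan changes.
- **The between-arm reading is inferred.** The recurrence objective does not mention groups, unlike the other secondary objectives, and the log-rank sentence does not name the arms. In a two-arm trial SR versus UC is still the natural reading.
- **Pooling is not fixed.** A reader might infer that the plan commits to one pooled curve and disregards AF type. The article states neither; it is silent on stratifying this test, and a fuller analysis plan may deal with it.
- **UC may also have rhythm reviews.** The article describes one within SR; it does not say that routine care lacks them.
- **No confirmatory claim is made.** The trial is sized for symptoms only, and nothing promises a causal conclusion from this outcome.
- **Noise dominates.** The largest simulated selection shift, ln(1.30) = 0.26, is smaller than the smallest standard error above, 0.38.

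These points narrow the concern without removing it. Stratifying by procedure in an unseen plan would deal with the mix, but would not restore randomisation in a subset formed afterwards. Imprecision is a further reason to treat the result as descriptive.

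**Conclusion.** The point holds in limited form. As stated, the analysis compares arms within a subset defined by a post-randomisation event that SR can plausibly affect, so its p-value is not a randomised test of SR on recurrence. This follows from the article's own sequence and definitions and depends on no assumed number.

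The size of any bias is unknown. In the 70%/50% illustration, mix alone gives a gap of about 11 percentage points under constant hazards and about 6 if all ablation recurrences fall in year 1. Selection alone moves the null rate ratio to between 1.08 and 1.30 in the unequal-uptake scenarios. A reader might take these, or the 6.7-fold hazard ratio, as estimates for this trial. They are not: the shares, uptake and severity effects are assumed, and the two recurrence figures come from separately cited sources with different time horizons. If uptake and mix proved alike in the arms, the bias would be small. The primary outcome is unaffected.

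**What to change.** In the analysis plan and the report:

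1. Label time to recurrence after DCCV or ablation as non-randomised and descriptive, and draw no causal conclusion about SR from it.
2. Tabulate the number, type and date of procedures by arm for everyone randomised.
3. Show the curves separately by procedure type, or stratify any log-rank test by it.
4. State that the randomised rhythm comparison is ICM AF burden, counted from randomisation, in all randomised participants with ICM data. AF burden is already the first secondary objective, so no new outcome is needed.

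The cost is some wording and one table. The Assessments list does not name procedure type and date, so the sponsor should confirm that both are recorded. Follow-up was still under way when the article was submitted. The downside is that one secondary p-value loses its between-arm causal reading, and with roughly 7 to 27 events under the assumptions above, separate or stratified curves will be imprecise.
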